### Statistical analysis

Statistical Package for the Social Sciences (
SPSS) version 18 will be used for the statistical analysis. The mean and standard deviation values will be calculated for each parameter and compared with the baseline and/or placebo. Differences between the baseline and/or placebo will be tested using a paired-t-test when data are normally distributed or Wilcoxon signed-rank when the data are skewed. The significance level will be set as a P value of ≤ 0.05.

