In an earlier study, we reported that daily supplementation of 200 mg TRF or α-tocopherol (α Toc) did not induce significant immunomodulatory changes in healthy human volunteers in the absence of any immunological challenge.
^
33
^ In a subsequent study, we included an immunological challenge in the form of tetanus toxoid (TT) vaccination in healthy individuals supplemented daily with 400 mg TRF. Daily supplementation of 400 mg TRF produced a significantly higher immune response to the TT vaccine.
^
19
^ A recent report showed that daily supplementation of 150 mg TRF for six months modulated some genes related to the immune system in healthy older adults.
^
34
^ In the literature, most studies have used a single dose of TRF to report their findings. To date, no studies have evaluated the dose-response effects of TRF supplementation on the host immune system. So, there is a need to evaluate the effectiveness of supplementing daily with lower doses of TRF (200, 100, or 50 mg) to boost immune response following an immunological challenge such as a vaccine. The influenza vaccine was chosen in this study as the vaccine model, as flu is a major problem faced by individuals worldwide.

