## Objectives

This study aims to investigate the effects of different concentrations of TRF (400, 200, 100 or 50 mg) on the immune response to an influenza vaccine in healthy individuals and to elucidate the mechanism of action. Using high and low dosages is important to understand what may happen following TRF supplementation. This information can be used to develop this in a range of functionality. The specific objectives are (i) to compare antibody responses to influenza antigen following daily supplementation with TRF (400, 200, 100 or 50 mg) with placebo; (ii) to compare leucocyte profiles and cytokine levels in response to influenza antigen following daily supplementation with TRF (400, 200, 100 or 50 mg) with placebo; (iii) to identify differentially expressed plasma proteins following daily supplementation with TRF (400, 200, 100 or 50 mg) with placebo in the presence or absence of vaccination; and (iv) to correlate plasma vitamin E levels with antibody levels in volunteers with and without daily supplementation with TRF.

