### Study hypothesis

The research hypothesis of this study is that daily supplementation of lower doses of TRF will enhance the host’s immune response to an influenza vaccine.

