## Discussion

At the start of 2020, a global public health challenge was caused by a novel coronavirus known as the severe acute respiratory syndrome coronavirus 2 (SARS-CoV-2).
^
37
^ This virus was named the novel coronavirus 2019 or COVID-19. COVID-19 was declared a pandemic by the World Health Organization (WHO) in March 2021. The pandemic has increased awareness of the need for a well-functioning immune system.
^
38
^
^,^
^
39
^ Nutritional interventions can potentially affect the host immune systems.
^
9
^
^–^
^
10
^ One such compound is vitamin E from palm oil. The vitamin E from palm oil is known as the tocotrienol-rich fraction (TRF), which contains tocotrienols (70%) and tocopherols (30%).
^
13
^
^,^
^
14
^ Several researchers have reported on the ability of TRF to modulate the host immune system. To the best of our knowledge, no studies investigated a dose-response curve using TRF supplementation and its impact on the host immune system. Previous studies have used high TRF concentrations, which may not be necessary to achieve the immune-enhancing effects in healthy individuals.

Furthermore, not many people may be able to afford a high dose of TRF. For any supplement, it is crucial to know what is happening biochemically at different dosages to understand the targeted effects as well as any side effects. It is important to use both high and low dosages in a study to fully understand what is happening in response to the intervention and develop this in a range of functionality. The influenza vaccine was chosen in this study as the vaccine model, as flu is a major problem faced by individuals worldwide.

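### The trial is justified by missing dose-response evidence, but the stated analysis makes no use of dose order, and one effect size taken from a 400 mg study sizes every arm

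*Protocol article*

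**What the plan says.** **Purpose.** The Introduction gives the reason for the trial: "To date, no studies have evaluated the dose-response effects of TRF supplementation on the host immune system". The Discussion repeats it: "no studies investigated a dose-response curve using TRF supplementation and its impact on the host immune system". Table 1 (Trial design) sets five equal arms of 30 at 0, 50, 100, 200 and 400 mg.

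**Formal question.** The hypothesis is that "daily supplementation of lower doses of TRF will enhance the host’s immune response to an influenza vaccine". Objective (i) is "to compare antibody responses to influenza antigen following daily supplementation with TRF (400, 200, 100 or 50 mg) with placebo", and objective (ii) makes the same comparison for leucocytes and cytokines. Objective (iv) is "to correlate plasma vitamin E levels with antibody levels in volunteers with and without daily supplementation with TRF".

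**Analysis.** The Statistical analysis section says: "The mean and standard deviation values will be calculated for each parameter and compared with the baseline and/or placebo". Differences "will be tested using a paired-t-test when data are normally distributed or Wilcoxon signed-rank when the data are skewed". It names no trend test, dose contrast or model across arms, and no method for the correlation in objective (iv).

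**Size.** The Sample size section gives 26 per arm for 80% power at 5% with d = 0.7 from an earlier study, raised to 30 for dropout. The Introduction attaches the same citation to the tetanus toxoid study of 400 mg. No separate effect is assumed for 50, 100 or 200 mg.

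**The concern.** Five ordered doses carry information on how response changes with dose. The stated analysis compares arms one at a time with baseline or placebo and discards that ordering. The lower doses are what is new here, since the protocol's own account is that 400 mg has already been tested with a vaccine challenge. Yet the only effect size behind the design comes from the top dose.

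If response rises with dose, a pattern of significance at 400 mg and not below it is quite likely even when the lower doses have real but smaller effects. The Discussion suggests that high doses may be unnecessary and unaffordable for many people, so a false negative at the lower doses would mislead on the practical question. Without estimates and intervals across the dose range, a reader could not tell an absent effect from an imprecise one.

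**Working it through.** **Inputs.** d = 0.7, 80% power, 5% level, 26 evaluable per arm (Sample size); five equal arms (Trial design). Sidedness is not stated. Effects at 50, 100 and 200 mg are not given, so the dose shapes below are assumptions.

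**1. Reproducing the stated 26.** For a two-sample t-test with n per arm, the non-centrality is d·√(n/2) = 0.7 × √13 = 2.52 on 50 df.
- One-sided 5%: power 80.1%; solving for 80% gives n = 25.9, so 26. This matches.
- Two-sided 5%: power 69.7%; solving for 80% gives n = 33.02, so about 33–34.
- A paired t-test (about 19 two-sided, 15 one-sided) and a five-group ANOVA at f = 0.35 (about 102 in total) do not give 26.

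Of the readings tried, only the one-sided two-sample comparison reproduces the figure.

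**2. Assumed standardised effects, holding d = 0.7 at 400 mg.**
- Linear: 0.7 × dose/400.
- Emax: 0.7 × [dose/(dose + ED50)] ÷ [400/(400 + ED50)].
- Plateau: 0.7 at every dose.

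| Shape | 50 mg | 100 mg | 200 mg | 400 mg |
|---|---|---|---|---|
| Linear | 0.088 | 0.175 | 0.350 | 0.7 |
| Emax, ED50 100 mg | 0.292 | 0.437 | 0.583 | 0.7 |
| Emax, ED50 50 mg | 0.394 | 0.525 | 0.630 | 0.7 |
| Plateau | 0.7 | 0.7 | 0.7 | 0.7 |

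**3. Power of each dose against placebo** (non-central t, 26 per arm, no multiplicity adjustment; two-sided / one-sided):

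| Shape | 50 mg | 100 mg | 200 mg | 400 mg |
|---|---|---|---|---|
| Linear | 6 / 9% | 10 / 15% | 24 / 35% | 70 / 80% |
| Emax, ED50 100 mg | 18 / 27% | 34 / 47% | 54 / 67% | 70 / 80% |
| Emax, ED50 50 mg | 29 / 40% | 46 / 59% | 61 / 72% | 70 / 80% |
| Plateau | 70 / 80% | 70 / 80% | 70 / 80% | 70 / 80% |

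**4. What a single trend contrast would add.** With scores c = −2, −1, 0, 1, 2 over the five arms, the non-centrality is Σcμ / √(Σc²/n) on 5 × 26 − 5 = 125 df. For the linear shape Σcμ = −0.0875 + 0 + 0.35 + 1.4 = 1.6625 and √(10/26) = 0.620, giving 2.68. Two-sided power:
- linear 76%, Emax ED50 100 mg 77%, Emax ED50 50 mg 75%, equal steps 80%;
- plateau 61%; only 400 mg active 61%;
- peak at 200 mg (0, 0.175, 0.35, 0.7, 0.35) 50%;
- peak at 100 mg (0, 0.35, 0.7, 0.35, 0.35) 20%.

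The contrast does well for graded monotone shapes and poorly for others.

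**5. If the trend test came first as a gate.** Simulated under the plateau with pooled-variance two-sided tests, power against placebo at 50–200 mg drops from about 71% to roughly 46–54%.

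**The case against.** The strongest reply is that the trial's formal question is not dose-response. Objectives (i)–(iii) and the hypothesis concern doses against placebo, and that comparison answers them directly. Dose-response language appears only in the Introduction and Discussion. This stands: a reader might infer that the trial cannot answer its own question, and the documents do not support that.

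A reader might also infer that the missing trend test causes low power. It does not. Any loss comes from sizing all arms on one effect combined with a graded curve, and adding a trend contrast leaves each single-dose test as powerful as before. Nor is low power a fact: under a plateau at 0.7 the one-sided comparisons have the planned 80%, and the suggestion in the Discussion that high doses may be unnecessary leans towards such a shape.

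A third tempting step is to make the trend the first confirmatory test. That fails. When only 400 mg works, the trend is still significant 61% of the time, so a positive result does not show that any lower dose works; used as a gate, it also costs power under a plateau.

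The planned plasma vitamin E correlation is an exposure-response element, so the protocol as a whole is not confined to placebo and baseline comparisons. But plasma level is measured after randomisation, and correlating it with antibody is not a randomised dose comparison.

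Finally, curve fitting is often left to a SAP, which is not shown. That softens the point without removing it: the section does name its comparisons and tests, and none of them uses dose order.

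**Conclusion.** The point holds in a limited form. The rationale and the five-dose design call for a dose-response analysis that the Statistical analysis section does not contain, and the power claim rests on one effect from a study described as 400 mg. Under the graded shapes assumed here every lower-dose comparison falls below the planned 80% whichever sidedness was meant, and far below it at 50 mg (6–29% two-sided, 9–40% one-sided). Under a common d = 0.7 there is no shortfall one-sided, and power is 70% two-sided. The documents do not say which shape applies, so the size is conditional. The dose-versus-placebo comparisons remain the right test of objectives (i) and (ii). What is missing is a supplementary estimate across doses and a plain statement of the assumption behind the power. This is an improvement worth making, not a flaw that invalidates the trial.

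**What to change.** In the Statistical analysis section:
- Keep the dose-versus-placebo comparisons as the test of objectives (i) and (ii), using between-group methods, since the arms are independent and the named tests are for paired data.
- Add a prespecified supplementary dose-response analysis of baseline-adjusted Day 56 antibody across all five arms, for example multiple contrasts with MCP-Mod, or a trend contrast plus a fitted curve. Report estimated effects with 95% CIs at 50, 100 and 200 mg.
- State that this analysis does not gate the placebo comparisons.
- State that a non-significant test alone will not be taken to show that a lower dose is ineffective.

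In the Sample size section, state that d = 0.7 is assumed at every dose and that the stated power does not hold if lower-dose effects are smaller.

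The cost is a few lines of text and some extra analysis, with no change to arms or numbers. The study status section places the trial at screening, so this could still be prespecified at that stage. The limitation to accept is that a single trend contrast is weak for plateau or non-monotone shapes (20–61% in the cases above), which is why it should stay supplementary and why several candidate shapes are preferable to one.

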### Outcomes

The primary outcomes of this trial will be comparing the antibody levels to influenza, the blood leucocyte profile, plasma vitamin E and cytokine production between the different groups. Secondary outcomes will be correlating plasma vitamin E levels with immune responses, plasma proteins and gene expression patterns.

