### Trial design

A single-centre, parallel, double-blinded, placebo-controlled with balanced randomisation into five arms (
Table 1).

**Table 1. T1:** Study groups.

Group	Daily supplementation (Day 0 to Day 56)	Number of volunteers	Influenza vaccine
A	Placebo (0 mg TRF)	30	Day 28
B	50 mg TRF	30	Day 28
C	100 mg TRF	30	Day 28
D	200 mg TRF	30	Day 28
E	400 mg TRF	30	Day 28
	Total volunteers	150	

TRF = Tocotrienol-rich fraction.

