### Study plan

Healthy subjects (n = 200-250) aged between 25 to 60 years old will be invited to participate in this study. At the time of screening, the purpose of the study and what the study entails will be explained to all volunteers who express an interest in joining the study. Before recruiting a subject for this study, a blood sample (12 mL) will be taken from all interested volunteers, where 10 mL of the blood will be sent to the Thomson Hospital medical diagnostic laboratory for various biochemical tests to establish baseline parameters to assist in the selection of healthy volunteers. The remaining 2 mL of blood will be used to quantify baseline plasma levels of vitamin E and anti-influenza antibodies. Then, 150 healthy volunteers who meet the inclusion and exclusion criteria (
Table 2) of this study, with the lowest level of anti-flu antibody and low plasma vitamin E, will be recruited for the study. Once a volunteer is selected for the study, a physician will explain the study protocol to the volunteer and ask the volunteer to provide a signed written informed consent to participate in this study.

**Table 2. T2:** Inclusion and exclusion criteria.

Inclusion criteria	Exclusion criteria
• 18–60 years-old • Healthy and free of diseases *(biochemical tests)*	• Have some health-related problems • On treatment or medication • Currently taking vitamin E supplements • Smoker • Received influenza A and B vaccination in the last 12 months • Obese (BMI > 35 kg/m ^2^) • Pregnant and/or breast-feeding

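### The plan assigns only paired tests to the comparison with placebo, although the five arms are independent parallel groups and the objectives are between-arm

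*Protocol article*

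**What the plan says.** Under Statistical analysis, the protocol article sets out two comparisons together: "The mean and standard deviation values will be calculated for each parameter and compared with the baseline and/or placebo". The next sentence names the test: "Differences between the baseline and/or placebo will be tested using a paired-t-test when data are normally distributed". For skewed data it gives the Wilcoxon signed-rank test. It names no other test, and no independent-samples test, ANOVA, ANCOVA or mixed model appears elsewhere in the article.

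The rest of the article describes a between-arm question:

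- **Trial design:** "A single-centre, parallel, double-blinded, placebo-controlled with balanced randomisation into five arms". There is no crossover and no matching. Table 1 gives the influenza vaccine on Day 28 to all five groups, placebo included.
- **Objectives:** the first is "to compare antibody responses to influenza antigen following daily supplementation with TRF (400, 200, 100 or 50 mg) with placebo". The second does the same for leucocyte profiles and cytokines.
- **Outcomes:** the primary outcomes are compared across arms; the list ends "plasma vitamin E and cytokine production between the different groups".
- **Sample size:** 26 per arm for a difference between groups, with d = 0.7, 80% power and 5% significance. With 15% dropout allowed for, 30 per arm are enrolled.

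**The concern.** A paired test needs a link between the two values in each pair. A volunteer's Day 0 and Day 56 values have one. A volunteer on 200 mg and a different volunteer on placebo do not.

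The sentence can therefore be followed in two ways. If the paired test is run across arms, someone has to invent the pairs. If it is kept to within-arm change from baseline, where it is valid, the randomised comparison has no test, and the wording (and/or) even lets the placebo comparison be skipped. For antibody at Day 56 and other influenza-stimulated responses, the within-arm change mixes any TRF effect with the response to a vaccine that everyone received.

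What is at stake is the trial's purpose, which is to say which lower doses enhance the vaccine response. Doses could be called effective because vaccination worked, or because one arm reached P ≤ 0.05 and placebo did not.

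**Working it through.** **1. Which test the plan's own sample size implies.** Inputs (Sample size section): d = 0.7, power 80%, significance 5%, 26 per arm. Sidedness is not stated. Solving the noncentral t power equation for n gives:

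| Test | n per arm (for the paired test, number of pairs) |
|---|---|
| Independent t, one-sided | 25.94, so 26 (power 80.1% at 26) |
| Independent t, two-sided | 33.02, so 34 |
| Paired t, one-sided | 14.07, so 15 |
| Paired t, two-sided | 18.03, so 19 |

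Of these, only the independent-samples test, one-sided, gives the stated 26. The trial was sized for a type of test that its analysis section does not name.

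**2. Paired test used across arms.** Take n = 26 per arm and arbitrary pairs.

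- *Error rate.* If pairs are formed without regard to outcome, the differences between independent people have mean zero under the null. In 20,000 simulated null trials the false-positive rate was about 5%.
- *Power.* A difference between two independent people has SD √2, so the paired effect size is 0.7/√2 = 0.495. Two-sided power is 67.9%, against 69.7% for the independent test.
- *Row order.* In five simulated pairs of arms with an unpaired p near 0.098, one arm was re-ordered 2,000 times each. The middle 95% of the paired p-values was about 0.04 to 0.16, and the middle half about 0.08 to 0.13. The same data can fall on either side of 0.05 depending on how the file is sorted.
- *Dropout.* 30 × 0.85 = 25.5 completers are expected per arm. Where two arms end unequal, the surplus people have no partner and are lost.

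**3. Paired test used within arm, Day 56 against Day 0.** Take n = 26, two-sided 5%, no TRF effect and the same vaccine rise s in every arm, in SDs of the within-person change. The documents give no size for the rise, so s is an assumption, shown over a range.

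- p = probability that an arm is significant against baseline: the power of a paired t-test with noncentrality s√26.
- q = probability that placebo is non-significant while at least one of the four TRF arms is significant: q = (1 − p)[1 − (1 − p)^4], the arms being independent.

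| Assumed rise s | p | q |
|---|---|---|
| 0.3 | 31% | 53% |
| 0.5 | 69% | 31% |
| 0.7 | 93% | 7% |
| 1.0 | 99.8% | 0.2% |

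For s = 0.5: q = 0.312 × (1 − 0.312^4) = 0.312 × 0.991 = 0.309.

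The two errors trade off. With a small rise, the danger is a false contrast between a significant TRF arm and a non-significant placebo arm. With a large rise, nearly every arm is significant, and the result says nothing about TRF.

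**The case against.** The strongest defence is that an article condenses its protocol and that a separate analysis plan may name the right test. That would excuse silence. It does not excuse this sentence, which assigns paired tests to the placebo comparison.

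Three further objections limit the point, and they stand:

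- **A reader might infer that the trial has no valid test at all.** The documents do not support that for the cross-arm reading. Step 2 shows that arbitrary pairing keeps its level and costs about two points of power. The defects there are arbitrariness and lost people. The misleading inference comes from the within-arm reading.
- **A reader might infer that every change from baseline is contaminated by the vaccine.** It is not. The vaccine is given on Day 28, so changes from Day 0 to Day 28 are not driven by it. Plasma vitamin E, listed as a primary outcome, is not obviously affected either. The argument concerns Day 56 antibody and influenza-stimulated responses.
- **A reader might infer regression to the mean**, because the Study plan section says volunteers "with the lowest level of anti-flu antibody and low plasma vitamin E, will be recruited for the study" and calls the screening sample baseline. However, the Laboratory tests section lists the samples of Days 0, 28 and 56 with Day 0 as baseline, and the gene expression text uses Day 0 against Day 56. Change is therefore not measured from the sample used for selection.

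**Conclusion.** The point holds and should be corrected before outcome data exist; the article reports the trial as still screening. The tests named do not fit the placebo comparison to which they are assigned, and they do not match the between-group calculation behind 26 per arm.

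This rests on the article's text and needs no assumption. The size of the harm does. Under the cross-arm reading it is a p-value that varies with row order, with little average loss of power. Under the within-arm reading with no TRF effect, the chance of a false contrast with placebo runs from 53% down to 0.2% as the assumed vaccine rise goes from 0.3 to 1.0 SD, while the chance that any one arm looks effective rises from 31% to 99.8%. The high ends of these two ranges belong to different assumed rises and cannot both apply. The figures take 26 completers per arm, two-sided 5%, normal data and an equal rise in all arms.

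**What to change.** Replace the sentence on paired tests with an independent-groups comparison of each TRF dose with placebo. The preferred form is ANCOVA of the Day 56 value on arm (five levels), adjusted for the Day 0 value, with antibody on the log scale. The minimum correction is an independent-samples t-test, or a Mann-Whitney test where data are skewed. Report each dose against placebo as a between-arm difference or ratio with a 95% confidence interval. Keep the paired t-test and signed-rank test for within-arm change, labelled as descriptive and not as evidence of a TRF effect.

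No new data are needed for antibody, since Day 0 is already sampled. The cost is a protocol change, which the Ethics consideration section says must be approved by the ethics committee before it is applied.

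The correction also exposes a separate matter: at d = 0.7 a two-sided independent t-test has 69.7% power with 26 per arm and 76.0% with 30. The sidedness should therefore be stated when the test is named.

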### Sample size

The sample size was calculated using
G*Power version 3.1.9.4. With the power set at 80% and a 5% level of significance, the analysis showed that 26 subjects per arm were required to detect a large difference between groups. The effect size (d) was assumed to be 0.7, based on a previous study.
^
19
^ Assuming a 15% dropout rate in two months, 30 subjects per arm (150 subjects) will be enrolled.

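### The test is chosen from the observed distribution and is paired even against placebo; one pre-set between-arm model adjusted for Day 0 would fit the trial better

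*Protocol article*

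**What the plan says.** The Statistical analysis section of the protocol article describes data by moments on the measured scale: "The mean and standard deviation values will be calculated for each parameter". It then gives one testing rule for two kinds of comparison, against baseline, against placebo or both. The rule is "a paired-t-test when data are normally distributed or Wilcoxon signed-rank when the data are skewed". The threshold follows: "The significance level will be set as a P value of ≤ 0.05". The section names no other test, no transformation and no covariate. It does not say how normality is judged, or whether the decision is made once per outcome, per visit or per arm.

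The Trial design section sets five parallel randomised arms, one of them placebo. The Sample size section plans for a contrast between arms: "26 subjects per arm were required to detect a large difference between groups", with "The effect size (d) was assumed to be 0.7". Under Laboratory tests, antibody levels are measured on Days 0, 28 and 56, so a pre-treatment value exists for each volunteer.

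**The concern.** The objectives compare each of four doses with placebo. Three features of the testing rule work against that.

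- **Paired tests for independent arms.** A paired t-test or signed-rank test needs two values from the same person, or from matched persons. A volunteer on TRF has no partner in the placebo arm, so neither branch of the rule fits that comparison.
- **Choice made from the outcome data.** The t-test concerns a mean change and the signed-rank test a rank-based shift. If the choice can differ between arms, 50 mg and 400 mg may be reported on different scales, and an apparent dose difference may partly reflect the test.
- **Day 0 is not used as a covariate.** A change score, or the Day 56 value alone, uses the Day 0 measurement less efficiently than adjustment does.

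At stake are a dose comparison on one scale, and some power in a trial that has little to spare.

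**Working it through.** **1. The plan's own figure.** Inputs from Sample size: d = 0.7, 80% power, 5% level (sidedness not stated).

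- Two independent groups, normal approximation: n = 2(z_α + z_β)²/d² per arm.
- One-sided: 2(1.645 + 0.842)²/0.49 = 25.2, so 26. The exact t calculation gives 25.94, so 26, with power 80.1%.
- Two-sided: 2(1.960 + 0.842)²/0.49 = 32.0, just above 32, so 33. The exact t gives 33.02, so 34. Power at 26 per arm is 69.7%.
- Paired designs give 19 (two-sided) or 15 (one-sided), so they do not match.

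The stated 26 is therefore an independent-groups figure, while the tests named for the analysis are paired. Below, 26 is taken as the evaluable number per arm and tests are two-sided at 5%.

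**2. Assumptions.** The article gives no SD, skewness or correlation. Levels are assumed lognormal with SD of ln 0.25 to 1.0, and Day 0 to Day 56 correlation r of 0.3 or 0.35 to 0.7. Normality is judged by Shapiro-Wilk at 5%.

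**3. How often arms would get different tests, if checked arm by arm.** If each arm passes the check with probability p, the chance that five arms do not all get the same test is 1 − p⁵ − (1 − p)⁵.

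| Data | p | Formula | Simulated |
|---|---|---|---|
| Raw data normal | 0.95 | 1 − 0.774 = 23% | 22% |
| SD of ln 0.25, r 0.5 | 0.887 | 1 − 0.549 = 45% | 45% |
| SD of ln 1.0, r 0.5 | 0.172 | 1 − 0.389 = 61% | 61% |

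The formula peaks at p = 0.5, at 1 − 2/32 = 94%. Over the lognormal settings the simulated share is roughly 40-93%.

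**4. Type I error between arms.** With independent-sample versions (t-test or Mann-Whitney chosen after the check), simulated rejection under no effect is 4.1-6.2%, against 4.6-6.5% for the log-scale adjusted model. With 1,500 runs the simulation standard error is √(0.05 × 0.95/1500) = 0.6 points, so there is no clear inflation.

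**5. Power between arms, true difference 0.7 SD on the log scale.** Adjustment for Day 0 shrinks the residual SD by √(1 − r²), so the effective effect is 0.7/√(1 − r²).

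- r = 0.35: 0.7/0.937 = 0.747, power about 75%.
- r = 0.5: 0.7/0.866 = 0.808, power about 82%.
- r = 0.7: 0.7/0.714 = 0.980, power about 93%.

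Simulation gives about 74-93% for the adjusted model and 64-92% for the test chosen after a normality check on change from Day 0. The gain is about 1-12 points. For example, with SD of ln 0.25 and a common rise of 0.4 SD, it is 74% against 64% at r = 0.35, and 93% against 92% at r = 0.7.

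**6. Where the gain comes from.** On the Day 56 value alone, the chosen test has 66-70% and a fixed log-scale t-test 68-71%, so fixing the log scale adds only about 0.5-4 points. Adding Day 0 raises power to 71-73%, 80-81% and 92-93% at r = 0.3, 0.5 and 0.7. Most of the gain is baseline adjustment.

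**7. Within-arm change.** The chosen test has 70-78%, against 78-81% for a fixed log-scale paired t-test: a loss of about 1-10 points, growing with skewness.

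**8. If raw data are normal.** There is no loss: 82% against 80% within arms, and 68% against 68% between arms.

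**The case against.** The strongest reply is that this is a condensed article. The normality criterion, the unit of checking and any transformation may sit in an analysis plan that is not shown. One decision per outcome, applied to all arms, fits the wording as well as an arm-by-arm check, and would remove the mixed-test problem. That stands: a reader might infer that doses will be judged by different tests, but the article does not say so, and the 40-93% applies only under the arm-by-arm reading. That share also counts any trial in which even one arm differs, and it does not measure changed conclusions. In a separate simulation the paired t-test and signed-rank verdicts disagreed in 2-3% of arms under no effect. With a log shift of 0.5 SD they disagreed in about 4-11% at SD of ln 0.4-0.6, and in 20% at 1.0.

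Lognormality is likewise an assumption. So is the correlation, and the Study plan narrows the Day 0 range by preferring volunteers with low anti-influenza antibody. If screening and Day 0 levels coincide, a correlation of 0.5 would fall to about 0.35-0.39, and 0.7 to 0.54-0.58. The power range above therefore starts at 0.35.

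What the reply does not remove is what the article does state: a rule driven by the outcome data, and paired tests assigned to a comparison with placebo. The placebo wording may be loose drafting, but the section names no other test for that comparison.

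**Conclusion.** The concern holds in a limited form. The sentence should be rewritten because its tests do not fit the comparison with an independent placebo arm, because it lets the data pick the test, and because it does not use Day 0 as a covariate. Mixed tests across arms are a possible result, not a stated one.

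The power at stake between arms is about 1-12 points at 26 per arm, assuming lognormal data, a 0.7 SD log-scale difference and a correlation of 0.35-0.7. Most of it is owed to baseline adjustment.

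Two stronger readings are not supported. The choice of test is not shown to inflate type I error once independent-sample versions are used. Nor does that choice alone cost much power between arms. A t-test on raw change regardless of skewness would have 59-82% (SD of ln 0.6-1.0), but the plan would drop that test when data are skewed, so this is not the plan's power.

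**What to change.** State one method in advance for antibody and cytokine levels:

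- Compare each TRF arm with placebo at Day 56 by a linear model on log values, adjusted for the log Day 0 value. Day 28 follows four weeks of supplement, so it is not a baseline.
- Report geometric mean ratios with 95% confidence intervals.
- Name one rank-based sensitivity analysis for independent arms, the same for all arms.
- Keep paired tests for descriptive within-arm change only.

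This replaces one sentence, needs no new data, and can be fitted in the software already named. The Study status section places the trial at screening, so the change can precede outcome data. The downside is that results are ratios rather than mean differences.
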